#### **B. Description of Population to be Enrolled:**

**Study setting.** To maximize the external validity of the proposed study, the project will be conducted within three large healthcare systems that care for diverse populations. These sites incorporate three states (Colorado, Maryland and District of Columbia) and two socio-economic groups (poor/uninsured and working/insured), and have sufficient minority patient populations to ensure that enrollment needs will be met.

**Denver Health (DH)** is an integrated safety net system serving the city of Denver. It consists of a 477-bed hospital and 9 community-based primary care clinics. The proposed study will be conducted at the Eastside, Park Hill, Webb, Lowry, Westside, and Level One Physicians clinics. Approximately 40 clinicians (physicians and advanced care providers) provide primary care at these clinics. In 2014, these clinics saw 23,831 patients in 64,757 outpatient visits. In these clinics, 8400 patients have hypertension, of which 37% are African American and 27% are white. Based on these data and our experience enrolling ~140 patients during our pilot study at a single DH clinic over 12 months, recruiting the targeted study sample is feasible.

**Kaiser Permanente of Colorado (KPCO).** KPCO is a not-for-profit integrated delivery system serving over 670,000 members at 22 outpatient medical clinics across the Colorado Front Range. Participants will be recruited from three KPCO clinics in order to assure adequate numbers of African American patients: East Denver, Aurora Centrepont, and Skyline clinics. In the first 2 quarters of 2015, these three clinics saw 71,582 patients; 12% were African American and 46% were white. Approximately 100 physicians and advanced care practitioners provide primary care at these clinics. In a recent hypertension study at KPCO there were 6,393 members with new prescriptions for antihypertensive medications over an 18-month period. A randomized trial of uncontrolled hypertension patients at KPCO enrolled 348 patients over 14-months. Based on these data, recruiting the targeted study sample is feasible.

**Kaiser Permanente of Mid-Atlantic States (KPMAS).** KPMAS is a not-for-profit integrated delivery system serving over 600,000 members in Maryland, District of Columbia and Northern Virginia. KPMAS has 32 medical centers across the service areas providing outpatient clinical care, as well as pharmacy and laboratory services. During the past year, 123,988 adult hypertensive patients, with at least one primary care visit, and continuous enrollment were identified at KPMAS. Among these hypertension patients, 33% were white and 48% African American. Recruitment will take place at 3 KPMAS medical centers in the Maryland and DC area which have large numbers of hypertensive patients with relatively balanced distributions by race: Capitol Hill, Kensington, and Gaithersburg Medical Centers. Our preliminary data indicates more than adequate population samples for successful recruitment at KPMAS.

**The collaboration structure.** All three sites have extensive experience with practice-based research and multicenter studies. DH and KPCO investigators have long-standing, ongoing collaborations, as have the KPCO and KPMAS investigators. Based on these experiences, we are confident the group can carry out the proposed work effectively. This multicenter collaboration will be further enhanced by a formal plan for training and supervision to ensure that enrollment targets are met, that study procedures are carried out with fidelity, and that data quality is addressed regularly. (see Data management plan)

**Patient eligibility.** Patients with a diagnosis of hypertension who have an upcoming clinic visit with their PCP will be screened on a weekly basis for inclusion/exclusion criteria using the electronic health record (EHR). Diagnosed hypertension will be defined as having an outpatient visit in the past 2 years with a primary or secondary ICD-9 code diagnosis of hypertension. This method of identifying patients with diagnosed hypertension has been shown to have a sensitivity of 81.4% and a specificity of 84.4% in a study done at DH; similar accuracy has been shown for Kaiser Permanente. Patients will be eligible if they have evidence for uncontrolled BP ( $\geq 140/90$  mm Hg) at least once at any point over the preceding 12-months. We have chosen a broad definition of uncontrolled BP since over 25% of patients with previously controlled blood pressure are no longer controlled over the following year. Recidivism to uncontrolled BP is associated with non-adherence. Additional inclusion criteria are age > 21 years, self-described race/ethnicity of (non-Hispanic) African American or non-Hispanic white, the ability to read and write English (self-reported), and the ability to provide informed consent. Patients with pregnancy-related hypertension or hypertension due to dialysis-dependent end-stage renal disease will be excluded as not being representative of the broader population of patients with chronic hypertension. Since pharmacy records are used for the primary measure of adherence, we will include those who obtain medications from DH, KPCO, or KPMAS pharmacies. Originally, we planned to exclude those who do not obtain medications from their home research site pharmacy. However, this has thus far prevented us from enrolling any white patients at our Denver Health site. Among those patients who do not obtain medications from their home research site pharmacies, we will seek consent to obtain medication fill data from their pharmacy of choice. At present, this constitutes nearly all patients seen at the study sites. We are aware that changes may occur as patients' benefit plans change. Using the electronic health record (EHR) at each site, we will be able to compare study patients with all hypertension patients to assess if this enrollment criterion has introduced bias.

Each site already uses its EHR to identify and track patients with hypertension for quality improvement purposes. The available data includes clinical characteristics (e.g. vital signs), demographics (including self-reported race, ethnicity, and language preference data), diagnoses, outpatient and hospital utilization, laboratory and imaging procedures, pharmacy records, death certificate data, and membership enrollment.

**Patient recruitment and procedures.** Subjects meeting inclusion/exclusion criteria will be contacted via mail, email, and/or phone prior to their scheduled appointment with

a PCP. Potential participants will be told the research is being done to assess adherence to hypertensive medications and to evaluate how a writing exercise about values might affect blood pressure. If they express interest in the study, they will be asked to arrive approximately one hour prior to the visit in order to review study procedures and provide informed consent. (see Patient Informed Consent) Those who decide to participate will have their blood pressure measured by the research coordinator using guideline-recommended procedures. Next, participants will be given a pre-randomized, consecutively numbered packet – to ensure the research coordinator is blind to the condition - containing the study materials. Packets will contain either an intervention or control version of the values affirmation exercise. To ensure balanced randomization by race at each site, there will be a pre-randomized series of packets for participants who self-identify as white and another pre-randomized series for those who self-identify as African American. Additional surveys will include a baseline demographics questionnaire, a measure of past experiences of discrimination, and a self-reported adherence (Voils) measure. (Table 1) Where patients feel comfortable using a tablet device, surveys will be administered and data will be collected on the tablet via an online survey format and stored in REDCap. If they do not feel comfortable with this format, all surveys will be administered on paper only. The values affirmation exercise will always be administered on paper, and the research assistant will provide instruction and remain available, but the patient will complete the exercise on their own, at their own pace. In our pilot work, patients completed all study materials in ~30 minutes. Next, patients will undergo routine check-in procedures, which includes blood pressure measurement at all sites, and complete the scheduled visit with their provider.

Following the visit with their provider, patients will complete the post-visit surveys that assess the proposed mediator variables, including 1) a standardized measure of patient activation, 2) a measure of attitude, perceived social norms, perceived behavioral control, 3) a measure of anticipated emotion regarding managing their blood pressure, and 4) a visit satisfaction survey. Patients will receive a \$20 gift card in compensation for participation. Participants must complete the values affirmation exercise in order to receive compensation for participation. Where patients are not able to complete all other surveys at the baseline/index visit, they will have the option of being contacted by study coordinators via phone to complete any remaining surveys, or to complete surveys via a direct web link to REDCap, that can be sent to them via email.

At 3-months, subjects will be called by the research assistant to schedule 3-month visit which includes measures of blood pressure, pill counts, self-reported adherence survey and the proposed mediators of the intervention effect (Table 1). This visit may coincide with a regularly scheduled follow-up visit with their provider. At 6-months, all subjects will return for an in-person visit to have their blood pressure measured by the research assistant and complete a 6-month survey with the same measures as those obtained at 3-months (Table 1). This visit may also coincide with a regularly scheduled follow-up visit with their provider. At the 3- and 6-month visits, patients will also be asked to bring all antihypertensive medications for pill count assessment, and will receive an additional \$20 gift card as compensation for participation. If patients are unable to attend either the 3 or 6-month follow up in person visit, they will be given the option to complete the surveys over the phone, or to complete surveys via a direct web link to REDCap that can be sent to them via email, and their incentive will be mailed to their home.

**Provider eligibility.** In secondary analysis, we will explore whether provider factors that have been associated with racial attitudes (*implicit racial bias, prior disparities training, self-efficacy regarding and interracial mix of clinical site*) influence the association between values-affirmation and adherence. All 200 primary care providers (physicians and advanced practice providers) at the participating 9 clinics will be eligible to participate. Based on our prior work, we anticipate a participation rate of ~60% of eligible providers (n=125). Since the provider measures will be considered separately, patients will be included even if their provider does not complete the survey.

**Provider recruitment and procedures.** Using methods our team has successfully used in studies surveying healthcare providers, all primary care providers at the participating clinics will receive a formal letter of invitation that includes a brief description of the study, benefits to them, and the endorsements of relevant administrators. The PI, co-investigator [name] and affiliated site co-investigator ([name] at DH, [name] at KPCO, [name] at KPMAS) will then present the project to groups of providers during a regularly scheduled department meeting. Based on our prior work, we know that one hurdle for participation will be busy schedules and therefore we have arranged with clinic directors to give the providers time from the meeting to complete the provider survey measures, online, in the privacy of their offices. Provider participants will receive a \$40 gift card code in their invitation letter which they may redeem for their time, and will be provided confidential feedback about their implicit racial attitudes immediately after completing the online survey. The participants will also be given scientific information about how they might minimize the influence of implicit ethnic/racial attitudes on their behavior.

Participants will access the secure website via the link provided in their invitation letter. At the website, they will enter the unique identifier provided to them in their invitation letter, and will then go through informed consent and complete demographic information along with measures of implicit racial bias, assessment of prior disparities training, and self-efficacy regarding caring for African American patients (see Provider Survey). The use of web-based technology will allow the providers to complete the measures privately, on their own schedule, and to retain the confidentiality of their participation. We anticipate providers' concerns about possible sanctions should their biases become known. To overcome these concerns, we will employ methods similar to those used in our prior work that include: 1) developing an elaborate system to ensure providers' complete anonymity, both in terms of their specific responses and with regard to whether or not they have participated; and 2) reassurance that their participation has the full backing of their organization.

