### IV. Research Methods

**Overall strategy.** We will conduct a randomized controlled trial in African American and white patients with uncontrolled hypertension, comparing a values affirmation intervention to a control exercise in three healthcare systems. The primary outcome will be change in medication adherence with secondary outcomes of change in blood pressure, time under blood pressure control and treatment intensification. We will explore the mechanistic effects of the intervention and assess the suitability of the intervention for more widespread dissemination.

- A. Outcome Measure(s):** The primary outcome measure is medication adherence comparing adherence before and after the intervention. The secondary outcome measures are systolic blood pressure (comparing blood pressure at the index visit to blood pressure at 6-month follow-up), time under blood pressure control and treatment intensification.

**Primary Outcome: Medication adherence.** We plan to measure medication adherence in three ways. First, we will assess adherence using electronic pharmacy records as in our pilot study. Computerized pharmacy records have been used in a wide array of studies to assess medication adherence and correlate with other adherence measures such as electronic adherence monitors, self-report, and pill counts, and with treatment outcomes such as BP control. The measure of interest for the proposed study will be a summary measure of adherence which assesses the proportion of days covered (PDC) over the period of observation for which a patient obtains antihypertensive medications. Adherence will be calculated for each antihypertensive drug in the regimen and combined across drugs into a summary measure of adherence for the entire drug regimen using the method developed by [name] et al. We will calculate prior adherence using data from 12 months prior to the index visit to calculate change in adherence compared with the six months after the index visit. The investigator team has used this method to measure adherence in prior studies.

Second, because some patients will have only one refill opportunity (90-day supplies) over the 6-month follow-up period, we will also collect self-reported adherence at baseline, 3 and 6-months using the validated Voils instrument. The measure has three questions that address the *extent* of non-adherence over the previous 7 days.

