### C. Study Design and Research Methods

[figure not shown]

**Overview:** The study design was developed in consultation with providers at the study sites to ensure feasibility of implementation in routine clinical practice. All primary care providers (PCP) at the participating clinics will be invited to complete a baseline survey regarding past disparities training and racial attitudes; patient participation will be independent of whether their PCP

participates. We will enroll self-identified African American and white patients with uncontrolled hypertension who are eligible and consent for the study. Our primary outcome is medication adherence that will be measured in three ways: 1) pharmacy fills, 2) self-report, and 3) pill counts. At the index visit, before they see their PCP, participants will have their blood pressure recorded and will complete a survey which includes a validated self-report measure of adherence (see Table 1 for survey contents). We will also query the EHR for baseline adherence based on prior 12-months pharmacy fills. Participants will be randomized to the values affirmation or control intervention tasks and they will complete the assigned task before seeing their PCP as scheduled. Following the visit, patients will complete a brief survey. Participants will return at 3-months and 6-months for in-person follow-up visits that will include assessment of adherence, blood pressure measurement and completion of surveys. Participants will be asked to bring all antihypertensive medications to each follow-up visit, and fill date and number of pills in the bottle will be recorded. Adherence will be calculated for each antihypertensive drug in the regimen and combined across drugs into a summary measure of adherence for the entire drug regimen. Secondary outcomes include blood pressure, time under blood pressure control, and appropriate treatment intensification. Throughout the study, we will evaluate the intervention for widespread dissemination based on the RE-AIM framework.

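### Late phone or web completion is not limited to the post-visit surveys, so a 7-day self-reported adherence form answered after the exercise can be filed as baseline

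*Protocol*

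**What the plan says.** Three parts of the Protocol fix when self-reported adherence is collected at baseline.

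- Section IV.A (Primary Outcome: Medication adherence) sets the schedule, "we will also collect self-reported adherence at baseline, 3 and 6-months", and says that the three items ask about the extent "of non-adherence over the previous 7 days".
- Section IV.C (Overview) gives the order at the index visit: "At the index visit, before they see their PCP, participants will have their blood pressure recorded and will complete a survey", and that survey contains the self-report adherence measure. Table 1 lists the adherence questionnaire and the prior-discrimination items in the pre-visit column.
- Section IV.B (Patient recruitment and procedures) describes the pre-visit set: "Additional surveys will include a baseline demographics questionnaire, a measure of past experiences of discrimination, and a self-reported adherence" measure. It then makes one item compulsory for payment: "Participants must complete the values affirmation exercise in order to receive compensation for participation". The next sentence opens "Where patients are not able to complete all other surveys at the baseline/index visit" and lets those patients be "contacted by study coordinators via phone to complete any remaining surveys", or finish through an e-mailed web link.

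On the role of the measure, Table 3 labels self-reported adherence a primary outcome. Section F (Statistical Analysis) names refill adherence as the primary outcome variable and treats self-report as a dichotomised secondary analysis.

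**The concern.** The late-completion sentence covers every survey except the exercise. It does not exempt the pre-visit forms, set a latest date, or say that a late form must be marked. A coordinator who follows it as written may collect the baseline adherence form by telephone days after the patient has done the exercise and seen the provider.

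That matters because the items look back only 7 days. A late form reports partly or wholly on behaviour after randomised treatment, yet would be stored as the baseline value. Any analysis that uses it as a starting point, whether as a change or as a covariate, would then use a post-treatment measurement. The protocol adds self-report because some patients have only one refill opportunity in the 6-month period, so it supports the refill measure where that measure is thinnest.

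The rule also reaches the prior-discrimination items. Section F plans a median split on those scores among African American patients who receive the intervention, with 120 per subgroup, as the main moderation contrast. A moderator should be measured before the treatment whose effect it is meant to modify.

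**Working it through.** **The timing rules side by side**

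1. Intended time of the adherence form: index visit, before the provider is seen (IV.C Overview; Table 1).
2. Permitted time: any later time, by phone or web, if it was not finished at the index visit (IV.B).
3. Time of the exercise: at the index visit, before the provider is seen (IV.C Overview).

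Items 2 and 3 together allow an adherence form to follow the exercise, which conflicts with item 1. Nothing in the document resolves the conflict.

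**How much of a late form is post-exercise**

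Input: a recall window of 7 days (IV.A). For a form completed d days after the index visit, the share of the window after the exercise is about min(d/7, 1).

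- d = 1: 1/7 = 14%
- d = 3: 3/7 = 43%
- d = 7 or more: 100%
- Later on the visit day: close to 0%, though the exercise or visit could still colour the answers

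**Averaged over all baseline forms**

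Let q be the share of forms completed late. The documents do not give q or d, so both are assumptions. The share of all baseline recall time that falls after the exercise is q × min(d/7, 1).

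- q = 5%, d = 1: 0.05 × 1/7 = 0.7%
- q = 10%, d = 3: 0.10 × 3/7 = 4.3%
- q = 20%, d = 7: 0.20 × 1 = 20%

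**Why this is not carried through to power**

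The sample size in section F is 240 per cell for an effect of 0.26 SD at 80% power, two-sided 0.05. It reproduces: n = 2 × (1.960 + 0.842)² / 0.26² gives 233 per cell, and 240 per cell gives power 0.81. That effect size was set for continuous refill adherence. Self-report is analysed as a dichotomy, and section F gives no effect size, change score or baseline adjustment for it. There is therefore no planned power figure from which a loss could be subtracted.

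**Prior discrimination**

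Table 1 puts these items before the visit, and the late-completion rule covers them too. They are modified from scales of lifetime discrimination related to healthcare (section IV.C, Prior experience of discrimination), so a delay of days hardly changes the period they describe. The recall-window calculation does not apply to them. The only issue is that the answers could be influenced by the exercise or the visit.

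**The case against.** The best defence is that the rule is a fallback and was probably meant for the post-visit surveys. It stands in the paragraph on those surveys, which are the longer set: a 13-item activation measure, the attitudes survey and a visit rating. Patients arrive about an hour early, the adherence form has three items, and pilot patients finished all study materials in about 30 minutes. Few adherence forms are therefore likely to be deferred. The protocol also promises a manual with collection instructions for each measure, and an SAP could say how late values are handled.

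Most of this limits the weight of the point without removing it. The sentence refers to all other surveys at the baseline visit, and that is the text staff at nine clinics would apply. A manual might tighten the rule, but the protocol would still say otherwise. An SAP can drop a late value but cannot recover a pre-exercise one that was never collected.

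Four stronger readings are tempting, and the documents do not support them:

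- A reader might infer that the primary analysis is compromised. It is not: its variable is pharmacy refills, with the 12 months before the index visit as baseline, and survey timing does not touch it. The primary-outcome label in Table 3 does not alter that.
- A reader might shrink the 0.26 SD effect by the late share, for example to 0.26 × (1 − 0.20) = 0.208 SD with power of about 0.62. The arithmetic is correct, but it borrows an effect size set for refill adherence, assumes a change-from-baseline analysis not stated for self-report, and assumes that every late form carries the full effect.
- A reader might conclude from the payment clause that patients short of time will defer this form in particular. The clause says only that the exercise is required.
- A reader might extend the 7-day argument to the discrimination items. Their lifetime basis rules that out.

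**Conclusion.** The point holds as a conflict between the stated pre-visit timing and an unrestricted late-completion rule. A self-reported adherence form completed d days late has about min(d/7, 1) of its recall window after the exercise and visit, and from day 7 it contains no pre-exercise information. It should not serve as baseline in the self-report analysis. This rests on the 7-day window and on reading the late-completion sentence as written.

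The overall size cannot be given, because the number of late forms and their delay are not stated. The setting suggests that there will be few. The consequence is confined to the self-report analysis and, for the separate reason of coloured answers, to the prior-discrimination moderator analysis. It is a modest defect, worth correcting because the repair is nearly free and a lost pre-exercise value cannot be restored.

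**What to change.** 1. In section IV.B, state that late completion by phone or web link applies only to the post-visit surveys.
2. Require the self-reported adherence and prior-discrimination items to be finished before the patient starts the writing exercise. Tie the rule to the start of the exercise and not to the opening of the numbered packet, because section IV.B says the packet holds the study materials.
3. Record the date and time of completion for each pre-visit form, in REDCap or on the paper form.
4. Treat any self-reported adherence value obtained after the exercise as a missing baseline. Leave late discrimination scores out of the moderator analysis, or flag them and examine them in a sensitivity analysis.

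The cost is a short change to the procedures, a completion time on each form, and a few missing baseline values. Section F already intends methods that use all available data. No sample-size figure changes.
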